### 2.6. Intervention method

#### 2.6.1. Experimental group.

The participants will participate in 36 outpatient rehabilitation exercise programs with incentives. Three CR sessions will be conducted weekly. The experimental group will receive 5000 (approx. 4 USD), 10,000 (7 USD), and 15,000 Korean Won (11 USD) per completed session of CR during the 1st to 12th, 13 to 24th, and 25th to 36th CR sessions, respectively. Participants who will complete the 36 sessions will receive ₩ 360,000 (260 USD) incentives.

#### 2.6.2. Control group.

The participants will participate in the same 36 sessions of outpatient rehabilitation exercise programs as those in the experimental group. However, the participants randomized to the control group will not receive incentives.

#### 2.6.3. Exercise program for both groups.

The CR program will consist of 36 outpatient sessions conducted over approximately 12 weeks. Each exercise session will consist of warm-up exercises (5–10 minutes), main exercises (30 minutes), and finishing stretching exercises (5–10 minutes). The main exercise will consist of aerobic exercise through a treadmill or ergometer under supervision, with the goal of reaching an exercise intensity of 70% to 85% of the baseline maximal heart rate. Drug compliance monitoring, appropriate nutrition, risk factor management, benefits of CR, and exercise education will be included.

#### 2.6.4. Adherence plan for participants.

All participants will be provided with a Galaxy Fit2(42 USD) Bluetooth Fitness Tracking Smart band after completing the assessment at 3 months to help them maintain self-care after completion of the CR program. All expenses of the follow-up assessments at baseline and 3, 6, and 12 months will be supported by funds provided by the Korea National Institute of Health, Korea Disease Control, and Prevention Agency, Cardiovascular Disease Department.

### 2.7. Study discontinuation criteria

Subjects who drop out or discontinue prior to the completion of the study are indicated as follows:

-When the participant withdraws consent to participate in the trial.-Violation of the selection criteria or falling under exclusion criteria.-When a researcher or clinical trial subject violates the study plan.-When a severe adverse event occurs in a clinical trial (e.g., hypotension, chest pain, and loss of consciousness).-If the researcher or clinical trial subject determines that it is necessary to terminate participation because of an adverse event.-Cases of disease recurrence.-If no data have been collected, because the study has never been assessed since randomization and when the subject cannot be tracked.-If it is determined that it is unreasonable to continue a clinical trial while the study is in progress.

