### 2.4. Binding and allocation

The control and experimental groups will be randomized, with each group having a 1:1 assignment ratio. Group assignments will be determined using computer-based random number generators and will be known only by the research assistant after opening a sealed envelope containing a computer-generated sequence sheet.

The participants will know which group they belong to; however, the assessor will not be aware of each participant’s group, and the participants will be instructed not to inform the assessor. The person managing the data will not know the subject group until the analysis of the study is complete. If any participant is included in the study discontinuation criteria, the principal investigator will reveal the blinding and progress to standard treatment.

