# Physical measurement: participation prior to exercise stress testing (including weight, BMI, etc).

** Exercise stress testing (including CPET test, VO_2_ peak, VO2 at anabolic threshold etc).

†† Subject questionnaire for PROM (KASI, physical activity, EQ-5D, and PHQ-9).

§§ Subject questionnaire for clinical outcome (including return to work, emergency room visits, and rehospitalization).

∥

∥ At the end of the 3rd and 12th months, the satisfaction assessment of the cardiac rehabilitation program is conducted through patient questionnaire.

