### 2.11. Statistical analysis

The analysis of this study was performed using an intention-to-treat and per-protocol method. CR participation, defined as the number of sessions completed, will be analyzed as a continuous variable using the student *t* test or Mann–Whitney *U* test, based on the normal distribution of the data. CR completion and categorical variables will be analyzed using chi-square or Fisher’s exact test. Missing data will be replaced using the last observation carried forward or the mean value. In the case of more than 20% of dropouts, missing data in the intent-to-treat analysis will be replaced using multiple imputations. The intention-to-treat population will include all enrolled participants, and the per-protocol analysis will include patients who have completed the 3-month evaluation.

Changes in secondary outcomes over time for the CPET, KASI, EuroQol 5 dimensions, and patient health questionnaire will be analyzed using paired t-tests with comparisons from baseline. Analyses will be conducted for each of the intervention, control, CR completion, and non-completed groups. For non-normal distributions, the Wilcoxon signed-rank test will be used.

Statistical significance will be set at *P* < .05, and SPSS version 20 (IBM SPSS Statistics, New York, NY) will be used for the statistical analysis.

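### Section 2.7 does not separate stopping the exercise program from stopping follow-up, so health-related discontinuations leave avoidable, informative gaps that weaken the ITT analysis

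*Protocol article*

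**What the plan says.** Section 2.7 opens with "Subjects who drop out or discontinue prior to the completion of the study are indicated as follows", so the list concerns the study and not only the exercise program. Four of its grounds matter here:

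- "When a researcher or clinical trial subject violates the study plan"
- "Violation of the selection criteria or falling under exclusion criteria"
- "When a severe adverse event occurs in a clinical trial (e.g., hypotension, chest pain, and loss of consciousness"), with a separate item for discretionary stopping because of an adverse event
- "Cases of disease recurrence"

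Section 2.4 gives the consequence: "If any participant is included in the study discontinuation criteria, the principal investigator will reveal the blinding and progress to standard treatment". It does not mention continued assessment.

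Section 2.8.1 says that, for patients who stop the assessments, values are used up to the point of dropout. Section 2.11 replaces missing data by last observation carried forward (LOCF) or the mean. Above 20% dropout it uses multiple imputation in the ITT analysis. It also states: "The intention-to-treat population will include all enrolled participants".

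Table 1 schedules CPET, patient-reported measures and clinical outcomes at 3, 6 and 12 months. Its footnote describes the last of these as "Subject questionnaire for clinical outcome (including return to work, emergency room visits, and rehospitalization").

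**The concern.** Recurrence and severe adverse events are health events. They are likely to affect later exercise capacity, quality of life, mood, emergency visits and readmission. If meeting a Section 2.7 criterion ends assessment, data are lost because of the patient's condition, in patients who could often still be reached. Values fixed before the event, or an average, would then stand in for data that could have been collected.

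The plan-violation ground adds a second problem. It has no threshold and covers a violation by the researcher as well as by the patient. The plan is 36 sessions at three per week, and attendance is the primary outcome. A site that read the ground literally could discontinue a patient for the behaviour that the trial measures.

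**Working it through.** **1. The plan's own numbers.** Inputs from Section 2.5: 55.4% versus 15.4%, power 0.80, 10% dropout. Alpha 0.05 is from Section 2.11, and two-sided testing is assumed. With pooled variance and p̄ = (0.554 + 0.154)/2 = 0.354:

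n = [1.960·√(2·0.354·0.646) + 0.842·√(0.554·0.446 + 0.154·0.846)]² / 0.40²
= (1.326 + 0.517)² / 0.16 ≈ 21.2, rounded up to 22 per group.

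This matches the stated 22. Dividing by 0.90 gives 22/0.90 = 24.4, against the stated 24. Power by the same approximation is 0.849 with 24 per group and 0.815 with 22. Because the ITT set keeps everyone and the session count needs no visit, loss of power on the primary outcome is not the main route of harm.

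**2. What happens to a discontinued patient.**

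| Step | Section | Rule |
|---|---|---|
| Event or violation | 2.7 | Patient is classed as leaving the study |
| Consequence | 2.4 | Unblinding, standard treatment |
| Data | 2.8.1 | Values used up to dropout |
| Analysis set | 2.11 | Patient stays in ITT |
| Gaps | 2.11 | LOCF or mean; multiple imputation above 20% dropout |

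No section provides for assessment after a Section 2.7 criterion is met. A patient discontinued before month 3 would lose all three post-baseline visits.

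**3. Which imputation applies.** The planned dropout is 48 × 0.10 = 4.8, about 5 patients. The multiple-imputation rule needs more than 48 × 0.20 = 9.6, so at least 10. At the planned rate the gaps are therefore filled by LOCF or the mean.

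**4. Scale.** One patient is 1/24 = 4.2% of an arm. The documents give no rate for recurrence or severe events. If 5% to 15% is assumed, 48 × 0.05 = 2.4 to 48 × 0.15 = 7.2, so about 2 to 7 patients.

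**5. Is non-attendance meant as a removal ground?** Taking the Section 2.5 rates as the proportion of patients completing, the plan expects 24 × (1 − 0.154) = 20.3 non-completers in the control arm and 24 × (1 − 0.554) = 10.7 in the incentive arm. That is 31 of 48, or 65%, against a planned dropout of 10%. Section 2.11 also plans comparisons from baseline within the non-completed group, which requires later assessments of those patients. The authors therefore treat non-attendance as an outcome. Section 2.7 does not say so.

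**6. Direction.** If the last value is the baseline one, LOCF gives zero change. That understates a gain in a patient who would have improved and hides a loss in one who worsened. Mean replacement pulls the patient to the average. The sign depends on the patient, the visit and the method chosen.

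**The case against.** The strongest reply is that this is detail that a journal article leaves to the full protocol. Section 2.7 never says outright that assessments stop, and Section 2.8.1 speaks only of patients who stop the assessments. That the loss follows from Sections 2.4, 2.7, 2.8.1 and 2.11 read together, and not from one sentence, is a fair limit. But the article does state a rule for leaving the study and attaches consequences to it, so the point concerns a rule as written and not a missing detail.

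Several stronger readings might be inferred, and the documents do not support them:

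- **That Section 2.7 contradicts the ITT set.** It does not. Section 2.11 keeps everyone enrolled and imputes, and Section 2.7 removes no one from an analysis set.
- **That control patients would be removed for not attending.** The dropout allowance and the planned analysis of non-completers point the other way.
- **That follow-up stops at the trial's named endpoints.** Emergency visits and rehospitalisation are collected but are not named in Sections 2.9.1 or 2.9.2, and recurrence is not a named outcome. CPET is a secondary outcome, however, and the patient-reported measures stand under the primary-outcome heading in Section 2.9.1, although Section 2.11 treats them as secondary.
- **That results would look better than they are.** No direction can be shown.
- **That never having been assessed is itself a ground.** That item is tied to patients who cannot be tracked, which is genuine loss to contact.

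Severe events are also reported to the IRB in any case (Sections 2.10.2 and 2.10.4). That serves safety but does not supply the missing outcome values.

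**Conclusion.** The point holds in a limited form. Section 2.7, read with Sections 2.4, 2.8.1 and 2.11, does not separate stopping the program or incentive from stopping follow-up. It therefore replaces obtainable CPET, patient-reported and clinical-outcome data with imputed values after health-related events. The ITT definition is intact, but the ITT analysis is weakened by missingness that is both informative and avoidable.

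Neither the direction nor the size of bias can be derived from the documents. The planned 10% dropout covers every reason, including withdrawal and loss to contact, so its roughly 5 patients cannot all be attributed to this rule. The range of 2 to 7 patients rests on an assumed event rate. The session count can stay complete if it is taken from attendance records. The plan-violation ground needs a clarifying sentence because, as written, it leaves open a reading that the rest of the protocol does not intend.

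**What to change.** Reconcile Sections 2.4, 2.7, 2.8.1 and 2.11 in one amendment:

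- State that meeting a Section 2.7 criterion may end the exercise program or the incentive but does not end data collection. Leave all clinical grounds for stopping exercise unchanged, including exclusion criteria that are contraindications.
- Take the session count from attendance records for every randomised patient.
- Continue the 3-, 6- and 12-month questionnaires and clinical outcomes, with CPET where the physician allows, unless the patient withdraws consent for follow-up or contact is lost.
- Do not use plan violation, or ineligibility found after randomisation, as a ground to stop data collection. State that missed sessions are outcome data and not a violation leading to discontinuation.
- Analyse all randomised patients in their assigned arm.

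The cost is the amendment and some extra effort to reach patients who stopped the program. The assessments are already scheduled in Table 1 and funded under Section 2.6.4.

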### 2.8. Data collection and analysis

#### 2.8.1. Assessment timing and assessment criteria.

All participants will complete baseline assessments and chart review (after consent), followed by assessments at 3 months after discharge (after the exercise program), and at 6 and 12 months after baseline evaluation (follow-up assessment) (Fig. 1).

**Figure 1. F1:**
[figure not shown]
Flowchart of the data collection.

During baseline assessment, basic demographic information (sex, age, body mass index, occupation, distance/time from home to the hospital, insurance type) and clinical information [cardiac arrest type, diagnosis, number of coronary artery stenosis/occlusion, intervention type/result, left ventricular ejection fraction (LVEF) (%), remaining coronary occlusion (%), lipid/glucose profile, echocardiogram findings, risk factor information (diabetes mellitus, hypertension, dyslipidemia, obesity), history of cardiocerebrovascular disease, laboratory results, body composition analysis and physical measurement, cardiopulmonary exercise testing (CPET) results, lifestyle risk factors (smoking, drinking, physical activity)] will be obtained through chart review. Additionally, basic information, patient-reported outcome measures (PROM), and clinical outcomes will be assessed.

At 3 months (assessment after completion of the exercise program), data will be collected on exercise therapy completion rate and the number of session participations.

At 3 and 6 months, body composition analysis, physical measurements, CPET results, PROM, and clinical outcomes will be assessed.

At 12 months, through chart review, echocardiography, laboratory test results, and medical information, if available, will be recorded, and body composition analysis and physical measurements, CPET results, PROM, and clinical outcomes will be assessed.

Patients who discontinue participation in the assessments during the study course will have values used in the analysis until the dropout period. All patients were sent an identical reminder text message informing the participants of the date, time, and location of the upcoming evaluation to promote patient retention and follow-up.

Table 1 presents the details of the data collection.

**Table 1 T1:** Schedule of enrollment, intervention, and assessments.

Timeline assessment item		① Consent	② Baseline	③ Exercise end point 3 months	④ 6 months	⑤ 12 months
Screening		√				
Enroll *		√				
Chart review †	Basic information		√			
	Occupation		√			
	Past history		√			
	Heart disease information		√			
	Cardiovascular imaging and detailed PCI Information		√			
	Echocardiography ‡		√			√
	Lab §		√			√
	Current medication		√			
	Cardiac rehabilitation information		√			
	KASI prior to the onset		√			
Intervention	Incentive		→			
Subject questionnaire (Assessment Index) ∥	Number of cardiac rehabilitation participation ¶			√		
	Body composition analysis and physical measurement #		√	√	√	√
	CPET results **		√	√	√	√
	KASI, EQ-5D, PHQ-9, and other PROM ††		√	√	√	√
	Clinical outcome §§		√	√	√	√
	Patient questionnaire ∥∥			√		√

CPET = cardiopulmonary exercise testing, EQ-5D = EuroQol 5 dimensions, KASI = Korean activity scale index, PCI = percutaneous coronary intervention, PHQ-9 = patient health questionnaire, PROM = patient-reported outcome measures, VO_2_ = oxygen consumption rate.

* Assignment of research number in order after obtaining consent.

† Chart review through medical records.

‡ Baseline: Preparation of initial trial results during hospitalization, 12-month results recorded if available in the medical record.

§ Baseline: Preparation of initial trial results during hospitalization, 12-month results recorded if available in the medical record.

∥ Questionnaires filled out by actual subjects.

¶ Record of participation in exercise program 36 times.

# Physical measurement: participation prior to exercise stress testing (including weight, BMI, etc).

** Exercise stress testing (including CPET test, VO_2_ peak, VO2 at anabolic threshold etc).

†† Subject questionnaire for PROM (KASI, physical activity, EQ-5D, and PHQ-9).

§§ Subject questionnaire for clinical outcome (including return to work, emergency room visits, and rehospitalization).

∥

∥ At the end of the 3rd and 12th months, the satisfaction assessment of the cardiac rehabilitation program is conducted through patient questionnaire.

### 2.9. Outcome evaluation

#### 2.9.1. Primary outcome.

The primary outcomes at 3 months will be the CR participation rate, defined as the number of CR sessions completed, and the CR completion rate (attendance of sessions greater than 50%; thus, completion of ≥ 18 sessions). Changes in PROM functional status using the Korean activity scale index (KASI), quality of life assessments in EuroQol 5 dimensions, and depression evaluation using the patient health questionnaire will be compared from baseline to 3, 6, and 12 months.

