#### 2.9.2. Secondary outcome.

The secondary outcomes at 3 months will be used to assess changes in cardiopulmonary endurance by 1 MET (peak oxygen consumption rate [VO_2_] 3.5 mL/kg/minutes), VO_2_ max, and VO_2_ at the anabolic threshold. At 6 and 12 months, improvement and maintenance of cardiorespiratory endurance by 1 MET (peak VO_2_ 3.5 mL/kg/minutes), VO_2_ max, and VO_2_ at anabolic threshold will be assessed.

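### Section 2.9.1 lists three patient-reported scales as primary that 2.11 calls secondary, and the two attendance primaries are each tested at .05 with no rule for success

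*Protocol article*

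**What the plan says.** Section 2.9.1 opens with two attendance measures: "The primary outcomes at 3 months will be the CR participation rate, defined as the number of CR sessions completed, and the CR completion rate", the latter meaning at least 18 of 36 sessions. Under the same heading it then lists "Changes in PROM functional status using the Korean activity scale index (KASI), quality of life assessments in EuroQol 5 dimensions". A third scale, for depression, completes that list, and all three are followed from baseline to 3, 6 and 12 months.

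Section 2.9.2 covers cardiopulmonary measures only, beginning "The secondary outcomes at 3 months will be used to assess changes in cardiopulmonary endurance by 1 MET". None of the three scales appears there.

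Section 2.11 says: "Changes in secondary outcomes over time for the CPET, KASI, EuroQol 5 dimensions, and patient health questionnaire will be analyzed using paired t-tests". It adds: "Analyses will be conducted for each of the intervention, control, CR completion, and non-completed groups". Sessions completed get a t test or Mann–Whitney test, and completion gets a chi-square or Fisher's exact test. One threshold serves all of these: "Statistical significance will be set at" P < .05.

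The abstract names the two attendance measures as primary and groups the three scales with cardiorespiratory function as further outcomes. Section 2.5 sizes the trial on one pair of rates, 55.4% against 15.4%, with power 0.8. That gives 22 per group, and 24 after dropout.

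**The concern.** There are two separate faults.

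- **Contradictory status.** The Korean activity scale index (KASI), EuroQol 5 dimensions (EQ-5D) and the patient health questionnaire (PHQ) are primary by placement in 2.9.1, absent from 2.9.2 and secondary by name in 2.11. A change in one of these scales could later be reported under either label.
- **No success rule.** Two attendance outcomes are both called primary and each has its own test at .05. The plan does not say whether the trial succeeds on either one or only on both. If either suffices, the chance of a false claim exceeds the stated 5%, and the sample size makes no allowance for this. If both are required, the error is controlled, but nothing in the text says so.

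In a trial of 48 people, what counts as success should be fixed before results are seen.

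**Working it through.** **1. Status of the three scales, section by section**

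| Place | Attendance outcomes | KASI, EQ-5D, PHQ |
|---|---|---|
| Abstract | primary (two) | further outcomes, unlabelled |
| 2.9.1 | primary (two) | under the primary heading |
| 2.9.2 | – | absent |
| 2.11 | tested between arms | secondary, paired tests from baseline |

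Sections 2.9.1 and 2.11 cannot both be right.

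**2. Reproducing the sample size in 2.5**

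Inputs from 2.5: p1 = 0.554, p2 = 0.154, power 0.80. Two-sided alpha of .05 is assumed, because 2.11 does not state sidedness.

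Formula (pooled variance, no continuity correction), with p̄ = (0.554 + 0.154)/2 = 0.354:

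n = [z(1−α/2)·√(2p̄(1−p̄)) + z(0.80)·√(p1(1−p1) + p2(1−p2))]² / (p1−p2)²

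- First term: 1.960 × √0.4574 = 1.3255
- Second term: 0.8416 × √0.3774 = 0.5170
- n = (1.3255 + 0.5170)² / 0.16 = 21.2, rounded up to **22 per group**, as stated

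Other variants: two-sided with continuity correction 26, two-sided unpooled 19, two-sided arcsine 21, one-sided without correction 17. One-sided with continuity correction also gives 22. Both routes to 22 use a single test at an unadjusted .05, so neither reserves alpha for a second primary outcome.

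**3. What an either-outcome rule would need**

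With Bonferroni at .025 each, the first term becomes 2.2414 × 0.6763 = 1.5158. Then n = (1.5158 + 0.5170)² / 0.16 = 25.8, rounded up to 26 per group. After 10% dropout, 26/0.9 = 28.9, so 29 per group or 58 in total, against the planned 48. Power for completion at .025 would be 72.1% with 22 per group and 76.5% with 24.

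**4. False-positive rate if either attendance outcome may win**

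If the two tests were independent: 1 − 0.95² = 9.75%. They are not independent, because both come from the same session count. The rate was therefore simulated under no incentive effect, with 24 per arm, a Mann–Whitney test on sessions and a test of completion at 18 or more. Attendance was assumed to be beta-binomial over 36 sessions, since the document gives no attendance distribution.

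| Test for completion | At least one P < .05 |
|---|---|
| Fisher's exact throughout | about 5.5% to 7% |
| Fisher's only when an expected count is below 5 | about 7% to 9% |
| Uncorrected chi-square throughout | about 7% to 10% |

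The choice of test matters at low completion. At 15.4%, the expected number of completers is 24 × 0.154 = 3.7 per arm, where Fisher's test would normally be used.

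**The case against.** The intended primaries can largely be recovered. The sentence in 2.9.1 that uses the word primary names only the two attendance measures, the abstract names the same two, the stated objectives are participation and completion, and 2.11 calls the scales secondary. This stands: the open question is how the two attendance outcomes combine, not which of many outcomes the trial is about.

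A reader might count two attendance outcomes plus three scales at three visits as 11 primary tests and infer a familywise error of 1 − 0.95^11 = 43%. The documents do not support that. Section 2.11 tests the scales by paired comparison from baseline within each of four groups, not between arms. Both arms could improve after infarction with no incentive effect, so a significant paired test is not a false positive for the trial's question. The 11-test calculation does not describe this plan.

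The inflation for two outcomes is also modest, and close to nominal if Fisher's test is used throughout. This stands too, but some excess remains in every variant, and 2.11 leaves the choice of test open.

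A success rule is often left to a statistical analysis plan. Here, however, the protocol itself names two primaries, fixes .05 for every test, and sizes the trial on one unadjusted test. A further document would not remove the conflict between 2.9.1 and 2.11.

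Finally, 2.5 speaks of a session-completion rate, which could mean the share of sessions attended rather than the share of patients completing. The two-proportion formula reproduces 22, and the section refers to low completion in Korea, so patient completion is the likelier meaning. It remains an inference.

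**Conclusion.** The point holds in two limited parts. First, the status of KASI, EQ-5D and PHQ is contradictory across 2.9.1, 2.9.2 and 2.11, which is plain from the text. Second, two attendance primaries are tested at .05 each with no stated rule. If either may count as success, the false-positive rate is about 5.5% to 10%, with 9.75% under independence.

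That range rests on assumed attendance distributions, two-sided testing and 24 per arm. It applies only to an either-outcome rule; if both outcomes had to succeed, there would be no inflation. It would be too strong to say that the error is several times nominal, or that the trial's question cannot be identified.

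**What to change.** 1. Move KASI, EQ-5D and PHQ from 2.9.1 to 2.9.2, and label them secondary in the abstract, so that the abstract, 2.9 and 2.11 agree.
2. In 2.9.1, name CR completion at 3 months (at least 18 sessions) as the single primary outcome, tested at two-sided .05. It is the outcome that 2.5 appears to size; 2.5 should say so explicitly.
3. Make sessions completed the first key secondary outcome, tested at .05 only if completion is significant.

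Requiring both attendance outcomes to be significant at .05 would also control the error. If that is the intention, it must be written down.

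The cost is a wording amendment and a registry update, made before the allocation is revealed for analysis. No extra patients are needed, since a single primary at .05 leaves the 22 per group in 2.5 unchanged. The small downside is that sessions completed cannot support a confirmatory claim if completion fails.
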